##### Attitude

Attitude toward engaging in physical activity is assessed using 3 items with a common stem [44,47], with responses provided on a 5-point semantic differential scale (eg, unenjoyable [1] to enjoyable [5]).

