##### Subjective Norms

Subjective norms in parents are assessed using 3 items referring to important others [44,47]. Children answered similar items, but in specific reference to family and friends separately. All items are scored on a 5-point Likert scale (1=strongly disagree to 5=strongly agree).

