##### Perceived Behavioral Control

Perceived behavioral control is assessed in both parents and children using 2 items [44,47], with responses provided on 5-point scales (1=strongly disagree to 5=strongly agree).

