##### Self-Monitoring

Self-monitoring toward physical activity is assessed using 2 items [44,48], each scored on a 5-point Likert scale (1=strongly disagree to 5=strongly agree).

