##### Habit

Habits are assessed using the 4-item automaticity subscale of the self-reported habit index [49,50], with responses provided on 5-point scales (1=strongly disagree to 5=strongly agree).

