### Data Analysis

Hypotheses will be tested using R software. All analyses will initially be performed as intention-to-treat, and per-protocol analyses will also be undertaken for comparison. Patterns of missing data will be explored using the Little missing completely at random test. Missing data in the final analysis will be inferred using full-information maximum likelihood analysis. We will test the efficacy of the intervention on our primary outcome, self-reported leisure-time physical activity, using an iterative series of generalized linear models. Independent variables will include time, intervention condition, demographic covariates (eg, start date, gender, and age), delivery group clustering, within-dyad clustering, and person-intervention theory fit *P*Δ [51]. Each variable group will be added in a subsequent iteration of the model, and model fit statistics will be examined at each iteration. This process will be repeated for each secondary outcome variable (perceived autonomy support, autonomous motivation, attitude, subjective norm, perceived behavioral control, action planning, coping planning, self-monitoring, and behavioral automaticity).

We also intend to assess the effect of theory-based mediators on change in physical activity using a path model. Specifically, we aim to assess whether the effects of intervention conditions on change scores in physical activity outcomes (both primary and secondary) are mediated by change scores in each of the psychological constructs targeted by the intervention (ie, perceived autonomy support, autonomous motivation, attitude, subjective norm, perceived behavioral control, action planning, coping planning, self-monitoring, and behavioral automaticity).

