This study tests a theory-based family behavioral intervention aimed at promoting change in physical activity participation in parent-child dyads. The intervention aims to foster autonomous motivation, enhance social support, and reduce perceived barriers to exercise in an atmosphere that is accepting and open. The intervention will make a unique contribution to practice and theory. Given the low levels of physical activity participation in adult and child populations, demonstrating the efficacy of web-based behavioral intervention in increasing physical activity that is both replicable and potentially scalable will make a valuable contribution to practice in health care contexts. In this research, we aim to enhance the potential usefulness of this intervention in the context of informing refined, scalable interventions based on results with the use of open materials and data, including intervention content and delivery guides. Further, from a scientific perspective, the application of a theory-based intervention developed in line with current practice intervention guidelines presents a potentially valuable test of mechanistic effects presented in the integrated behavior change theory and its component models [12-15], identifying the “active ingredients” of the intervention that are associated with desired outcomes. That is, while the integrated behavior change theory has been supported in several correlational studies [22,23,52], such research only provides an indication of the likely variables most important in determining behavior and can by their correlational nature not be used for any assertions of direction or causality. Thus, a key contribution of this intervention is assessing not only whether the program is successful in changing behavior, but also in assessing which target constructs mediate the effects of the intervention on behavior change and may therefore be most valuable when refining current strategies or developing new programs.

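### Change-score mediation loses precision in the randomised condition-to-mediator path, and its indirect effects cannot be compared across constructs without scale reliabilities

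*Protocol article*

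**What the plan says.** The Data Analysis section of the protocol article states the intention to "assess the effect of theory-based mediators on change in physical activity using a path model". Both sides of the model are change scores: activity outcomes on one side and, on the other, effects are "mediated by change scores in each of the psychological constructs targeted by the intervention". Nine constructs are listed as mediators. No measurement model or correction for measurement error is mentioned.

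The Outcomes section gives short scales of differing length:

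- Two items: "Perceived behavioral control is assessed in both parents and children using 2 items" and "Self-monitoring toward physical activity is assessed using 2 items".
- Three items: "Attitude toward engaging in physical activity is assessed using 3 items with a common stem" and, for parents, "Subjective norms in parents are assessed using 3 items referring to important others".
- Four items: autonomous motivation, and habit ("Habits are assessed using the 4-item automaticity subscale").

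No reliability, inter-item correlation or pre-post correlation is given for any scale.

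Under Potential Findings and Implications, the Discussion says what the result is for: to learn "which target constructs mediate the effects of the intervention on behavior change and may therefore be most valuable when refining current strategies".

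**The concern.** A change score carries the measurement error of two occasions and discards the part of the true score that is stable. This acts differently on the two halves of an indirect effect.

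In the condition-to-mediator path, randomisation makes the estimate unbiased with or without baseline adjustment. The only issue is precision, and an unadjusted change score gives some away.

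In the mediator-to-activity path, error in the mediator pulls the coefficient towards zero, more for a scale that measures change less reliably. Two mechanisms of equal strength can then show unequal indirect effects. Because the Discussion intends to use the results to choose which constructs to build on, a difference in measurement quality could be read as a difference in mechanism.

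**Working it through.** **Inputs.** From the article: change scores in a path model (Data Analysis); 2 to 4 items per scale where stated (Outcomes); 178 people expected to be analysed (Power Analysis). The last figure agrees with the recruitment target: 254 × 0.70 = 177.8. The article gives no figure for mediation. Everything below on reliability, stability and correlation is therefore an assumption, shown as a range.

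**1. Condition-to-mediator path.** Let r be the pre-post correlation of the observed score, with equal variance σ² at both times.

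- Variance of a change score: 2σ²(1 − r).
- Residual variance after baseline adjustment: σ²(1 − r²).
- Ratio: 2(1 − r)/(1 − r²) = 2/(1 + r).

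| r | ratio | 178 ÷ ratio |
|---|---|---|
| 0.3 | 1.54 | 116 |
| 0.5 | 1.33 | 134 |
| 0.6 | 1.25 | 142 |

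For this path, an unadjusted change score from 178 people is worth an adjusted score from about 116 to 142. This count treats people as independent and ignores dyad and delivery-group clustering.

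**2. Mediator-to-activity path.** Let rel be the scale's reliability and s the stability of the true score from baseline to follow-up.

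Reliability of change = (1 − s)·rel / [(1 − s)·rel + (1 − rel)]

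For assumed reliabilities of 0.65 and 0.80 and the same s for both:

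| s | rel 0.65 | rel 0.80 | ratio |
|---|---|---|---|
| 0.4 | 0.39/0.74 = 0.527 | 0.48/0.68 = 0.706 | 1.34 |
| 0.6 | 0.26/0.61 = 0.426 | 0.32/0.52 = 0.615 | 1.44 |
| 0.8 | 0.13/0.48 = 0.271 | 0.16/0.36 = 0.444 | 1.64 |

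**3. What baseline adjustment does to that gap.** If activity depends on the follow-up level of the construct, the attenuation factor is 1 − (1 − rel)/(1 − r²), with r = s·rel. At s = 0.6 this is 1 − 0.35/0.848 = 0.587 and 1 − 0.20/0.770 = 0.740, a ratio of 1.26. Over s = 0.4 to 0.8 the ratio is 1.24 to 1.27. The gap narrows but does not close. If activity depends on true change instead, the adjusted coefficient is attenuated by (rel − r)/(1 − r), which is the change-score reliability again, so nothing is gained.

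**4. Illustration of the consequence.** A simulation used three mediators with identical true paths (indirect effect 0.100 each), 178 independent people, inter-item correlation 0.5 for every scale, true stability 0.6 and uncorrelated mediators. For 2, 3 and 4 items, the mean indirect effects were 0.045, 0.054 and 0.061, and detection rates were 25%, 33% and 38%. The condition-to-mediator estimate averaged about 0.40 at every length. The loss is therefore bias in the second path only.

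**The case against.** **Change scores have a merit in the second path.** The mediator-to-activity relation is not randomised. With change scores on both sides, a stable person or family trait that affects mediator and activity equally at each time cancels out. Adjustment for an error-prone baseline does not remove it. In simulations with such a trait and no true mediator effect, change scores returned about 0.00. Baseline adjustment returned a spurious 0.06 to 0.07 under one set of assumptions and 0.11 to 0.19 under another. This objection stands: replacing the change scores throughout would exchange attenuation for a possible false mediator.

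**A reader might infer that the two-item constructs are bound to be penalised most.** The article does not support that. Reliability depends on inter-item correlation as well as length: two items correlating 0.67 give 2 × 0.67/1.67 = 0.80, the same as four items correlating 0.50 (4 × 0.50/2.50 = 0.80). No correlations are reported, and three of the nine mediators have no stated item count.

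**A reader might also infer a two- to four-fold gap.** That follows from holding the observed retest correlation equal across scales of reliability 0.65 and 0.80. Equal observed correlation implies unequal true stability: at 0.5 it is 0.5/0.65 = 0.77 against 0.5/0.80 = 0.625, and at 0.6 it is 0.92 against 0.75. Those are no longer equally changeable constructs.

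**Details may sit elsewhere.** The article says only change scores in a path model. It does not exclude a measurement model in a fuller plan, and it sets out no formal ranking of indirect effects. Constructs are also compared by condition in separate secondary-outcome models. This limits the weight of the point, but the Discussion's intended use still invites comparison between constructs.

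**Conclusion.** The point holds in a limited form.

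- **Firm:** in the randomised path, unadjusted change scores cost a factor of 2/(1 + r) in variance, 1.25 to 1.54 for r of 0.6 to 0.3. This needs only equal variances and a value for r. It is a loss of precision, not a bias.
- **Conditional:** in the mediator-to-activity path, attenuation differs between scales in line with their reliabilities. Under the assumed 0.65 and 0.80 with equal true stability of 0.4 to 0.8, change-score reliability differs 1.34- to 1.64-fold. Which constructs lose most cannot be said from the article.
- **Not supported:** that change scores are an error to be removed from the whole model, or that scale length alone settles which constructs are under-rated.

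The primary efficacy comparison and the sample size are unaffected.

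**What to change.** In the Data Analysis section:

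1. Add the baseline score of the same construct as a covariate in each condition-to-mediator equation. The change score can remain the dependent variable, because once baseline is in the equation the condition effect is the same as for the adjusted follow-up score.
2. For the mediator-to-activity path, keep the planned change-score estimate and report beside it an estimate from follow-up scores adjusted for baseline construct and baseline activity. State that the first is exposed to stronger attenuation and the second to stable shared confounding. Agreement between them strengthens a conclusion, and disagreement should be reported as such.
3. Report each scale's reliability next to its indirect effect.
4. State that constructs will not be ranked as active ingredients on indirect effects uncorrected for measurement error.

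The cost is one covariate per condition-to-mediator equation, one additional set of estimates and some reporting. No new data, measures or participants are needed.

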### Ethical Considerations

All study procedures have been approved by the University of Jyväskylä Human Sciences Ethics Committee (statement number 806/13.00.04.00/2023). All parents interested in participating in the study will be presented with detailed information about the intervention, potential risks to participants, the right to withdraw, and data security arrangements. Parents will have the chance to read this information and ask questions of the research team before providing their informed consent to participate. Data will be stored on secure cloud-based servers hosted by the University of Jyväskylä consistent with our data archiving and storage management plan, compliant with university guidelines. At the conclusion of data collection, participants’ physical activity and data on psychological measures at each measurement point will be matched using pseudonymized codes and deidentified to the greatest extent possible. Participants will not be offered any financial or other compensation for their participation.

## Results

The project team received final notification of research funding approval for the current project from the Finnish Ministry of Education and Culture, Sport Science Funds, in March 2022 (PROJECT 350904), and the trial has been preregistered on ClinicalTrials.gov (ID 806/13.00.04.00/2023). Enrollment into the trial commenced on September 20, 2023. Enrollment is scheduled to continue until March 2024, with the final collection of follow-up data scheduled for December 2024.

We expect that the research will provide valuable formative evidence for the efficacy of a theory-driven family-based physical activity intervention strategy. Further, as the proposed trial includes open materials and tests of the theory-driven mechanistic effects that may encourage behavior change, this research may also serve as a valuable stepping stone to the development of more large-scale, low-cost interventions for family behavior change.

## Discussion

### Overview

This protocol presents a randomized controlled trial aiming to increase physical activity levels in inactive parent-child dyads within Finland, based on the integrated behavior change model. We hypothesize in this protocol that both parents and children will show increased levels of physical activity, our primary outcome variable, both at the immediate and 3-month postintervention stage, relative to a waitlist control group. Further, we hypothesize we will observe similar changes in the trial’s secondary outcomes, the psychological constructs of the integrated behavior change model (ie, autonomy support, autonomous motivation, attitude, subjective norm, perceived behavioral control, self-monitoring, intentions, and habit), in the intervention group relative to the waitlist control group.

### Potential Findings and Implications

Children transitioning into adolescence have shown a sharp decline in activity levels [3], while parents are generally less active than similar adults without children [8]. Thus, both populations individually represent valuable targets for intervention. Recognizing this, governments and health departments have recommended behavioral interventions to promote physical activity participation in both groups. However, beyond strategies to influence physical activity in either children or parents separately, research indicates that parents and children likely have a noteworthy influence on each other’s physical activity behaviors and beliefs [6,7,9]. Thus, the delivery of interventions in family contexts, such as parent-child dyads, represents a potentially highly valuable strategy to promote physical activity participation in both populations. This is supported to a degree in meta-analysis, as dyadic interventions encouraging an active lifestyle demonstrated slightly larger effects than those targeting individuals [10]. Yet, such interventions remain relatively rare compared to more traditional, individual-targeted programs, particularly those that are based on behavioral theory which may contribute to their efficacy and relevance to health sciences overall [10].

This study tests a theory-based family behavioral intervention aimed at promoting change in physical activity participation in parent-child dyads. The intervention aims to foster autonomous motivation, enhance social support, and reduce perceived barriers to exercise in an atmosphere that is accepting and open. The intervention will make a unique contribution to practice and theory. Given the low levels of physical activity participation in adult and child populations, demonstrating the efficacy of web-based behavioral intervention in increasing physical activity that is both replicable and potentially scalable will make a valuable contribution to practice in health care contexts. In this research, we aim to enhance the potential usefulness of this intervention in the context of informing refined, scalable interventions based on results with the use of open materials and data, including intervention content and delivery guides. Further, from a scientific perspective, the application of a theory-based intervention developed in line with current practice intervention guidelines presents a potentially valuable test of mechanistic effects presented in the integrated behavior change theory and its component models [12-15], identifying the “active ingredients” of the intervention that are associated with desired outcomes. That is, while the integrated behavior change theory has been supported in several correlational studies [22,23,52], such research only provides an indication of the likely variables most important in determining behavior and can by their correlational nature not be used for any assertions of direction or causality. Thus, a key contribution of this intervention is assessing not only whether the program is successful in changing behavior, but also in assessing which target constructs mediate the effects of the intervention on behavior change and may therefore be most valuable when refining current strategies or developing new programs.

### Limitations

Beyond the expected value presented by the research, it is also important to note that the trial faces some expected and inherent challenges and limitations. For example, as the intervention does not include any reward or payment to participants beyond the benefits of the intervention itself, it is likely that parents who consent to enroll themselves and their child in the program will already be at least somewhat motivated to change their physical activity behavior. Such an issue has been noted in the previous parent-for-child interventions [53]. If this is the case, it is likely that the intervention effects will not be as strong as expected, as already motivated participants possess a lesser degree of potential for change than might be expected in families with unmotivated parents. While this nonetheless poses a challenge to the intervention, it is important to note that motivation or knowledge of the need for physical activity is commonplace [9,54], even as actual activity levels remain low. As the strategies used in this intervention include training parents in autonomy support rather than controlling strategies that may inhibit their child’s autonomy and thus harm the development of active lifestyles [20,55], as well as strategies to bridge the intention-behavior gap, this trial still has bona fide value in targeting this key population. However, the problem of accessing and enrolling unmotivated families into intervention programs remains a concern for behavior change research.

### Conclusions

Given the generally low levels of physical activity in Finnish parents and children, there is a notable need for intervention strategies aiming to encourage an active lifestyle in these populations. This protocol presents an upcoming randomized control trial based upon the integrated behavior change model, which aims to use a series of web-based, theory-based behavior-change strategies delivered to both parents and children as a dyadic program. In doing so, the proposed trial aims to extend upon current literature in several key aspects. First, by targeting parents and children as a dyad, the proposed study aims to add to the available literature on whether physical activity behavior change programs may be more efficacious when targeting the family unit, rather than parents or children individually. Second, as this study uses a theory-based design, testing change in both physical activity and related psychological constructs, the trial also offers an opportunity to test which beliefs and psychological factors are most associated with concomitant change in physical activity. These data, combined with the trial’s open materials, may thus serve as a valuable stepping stone to the development of more large-scale, low-cost interventions for family behavior change.

## Appendix

Multimedia Appendix 1 Peer review report from the Finnish Ministry of Education and Culture.
